### 2.5. Number of Clusters

The minimum number of units to be able to achieve a 5% level of significance is four per arm assuming normality for the cluster level responses and the use of non-parametric test, Mann–Whitney *U*-test [24]. Campbell [31] further states that with three units per arm, it is within the bounds of chance that the outcomes in the three treatment arms are all greater than the outcomes in the three control arms; however, with four per arm, this is unlikely to happen by chance more than 1 in 20 times. Therefore, the minimum number of clusters is four per arm (eight in total) for an unmatched design or six matched pairs for a matched design.

**To determine number of clusters needed (*n*_cluster):**
*n*_cluster = Total number of participants in the two groups (/fixed cluster size) = (*^n^*_Cluster_Binary × 2)/*m*_ = 988/60 = 16.5 ~17 clusters. 

In order to have the same number of clusters per arm, the number of clusters was increased to the nearest upper even number, which is 18 in this study. Therefore, the study will have a total of 18 clusters; nine clusters will be randomized to the intervention and nine clusters will be randomized to control group. This means that the sample size contains 1080 adolescent girls in 18 clusters.

### 2.6. Sampling Techniques

The study will use multi-stage sampling technique to select the study population. The Hoima District was purposively selected because of the high (29%) adolescent pregnancy and the thriving economic activities, which further increase the vulnerability of the adolescent girls to pregnant. The District has 36 registered secondary schools in four constituencies Kigorobya, Bugahya, the Hoima municipality and the Buhaguzi counties.

**Cluster Sampling:** Clusters of adolescent girls attending secondary school who represent the target population will be identified and included in the sample [34]. This will be used to increase the level of efficiency of sampling and each cluster will be considered as a sampling unit. In this study, the clusters will be secondary schools registered and operational in the Hoima District; a list of all clusters (schools) will be generated from the District Education Office and clusters will be ranked according to the level of school dropout rate. The top 18 clusters (schools) with the highest dropout rate will be considered for the study. The selection will be based on the judgment of the researcher using drop-out rates at each school within the population in the Hoima District. The schools to be selected from each county should rank highest in dropout rates of adolescent girls in the last 12 months prior to the study. Four to five secondary schools with the highest student enrolment and highest school dropout rates will be selected from each county. The statistics will be derived using the annual school dropout reports from the Hoima District Education Officer (DEO) and the Chief Administrative Officer (CAO). In addition to the school dropout rates, the schools to participate in the study will meet the following requirements:Permission to conduct outreach SRH services at school and willingness of the head teacherAvailability of SRH focal person usually called the ‘senior woman teacher’Proximity to a functional public health center (within 5–10 km)Access to eligible studentsGeographical location of the school

**Random Sampling:** The allocation of schools (clusters) to either the intervention and control groups will be randomly conducted. After selection of the 18 schools, nine schools will be randomly allocated to the intervention group and the other nine will be allocated to the control group. The names of the 18 selected schools will be placed in a basket and randomly selected and allocated to either group of study.

Blinding will be conducted at the random allocation of the school clusters to either the intervention group or control group. The research assistants, Biostatistician and school administration will be blinded to the study hypotheses.

**Systematic Sampling:** Systematic sampling will be used to select the 1,080 adolescent girls from the 18 schools (clusters). This is a probability sampling method in which sample members from a larger population are selected according to a random starting point and a fixed periodic interval [33]. Upon selection of the 18 schools that are considered to be clusters, 60 eligible girls will be systematically selected from each school using class lists.

A list of all girls aged 15–19 years in form two, three and five will be generated by the school administration. This periodic interval will be determined beforehand as 2, which means that assuming the starting point is 1 as the first serial number on the class lists, every girl with an even serial number will be selected to participate in the study, that is, 2, 4, 6, 8, etc. The girls will have an equal chance to be selected to participate in the study. A total of 1080 secondary school girls will be systematically selected from the 18 schools in equal numbers of 60 girls aged 15 to 19 years per school. Figure 1 illustrates the sampling framework to be used during the study.

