## 2. Methodology

The study will use an experimental research design to assess the effect of the school-based SRH services on occurrence of the adolescent pregnancy among the school girls aged 15–19 years. The Cluster Randomized Controlled Trial (CRCT) design with qualitative and quantitative components will be used as a gold standard in conducting this impact evaluation research so as to maximize comparability between the intervention and control groups, and hence give a strong evidence of a causal relationship between the intervention and the outcome [30,31,32].

The unit of randomization will be the 18 clusters (school) and 1080 individuals (girls); therefore, the cluster (school) of the eligible girls will be randomly allocated to either the intervention (9 schools) or the control (9 schools) arms of the study.

Blinding will be done to prevent systematic biases stemming from foreknowledge of group allocations among the participants and research aim outcomes as per RCT study standards [31]. Pre-determined information, such as the research hypothesis, will be concealed from the participants, data collectors, teachers and data analysts so as to prevent biases at all levels of the research. The participants will not be made aware of the research hypothesis and will be assigned any group accordingly.

In order to avoid misleading biases, the study will use the Intent To Treat (ITT) approach for analysis. Every participant allocated to a treatment group is considered to be part of the trial. ITT will be used in an attempt to avoid potential bias and identify the true effect of the intervention.

The research will use a pre-test-post-test control group approach [33]. This is where pre-intervention (baseline) measures on the prevalence of pregnancy will be conducted to allow for explicit evaluation of the pre-to-post changes.

Qualitative data will be collected through in-depth interviews of key informants in the community and discussions with groups of adolescent boys, parents, community members and school leadership. Standard guides with open-ended questions will be used for conducting the interviews and discussions. The participants of the interviews and discussions will be purposively selected based on their role in preventing adolescent pregnancy in the community.

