### 2.7. Recruitment of Study Participants

The study will be conducted in the 18 selected secondary schools as clusters; each school will be randomly assigned to the intervention study group or the control study group. Each school cluster will be independent, with no crossover of staff/students and defined as a natural cluster for the purpose of the trial. Each arm of the study will have nine schools (clusters).

The selection of the 18 study schools (clusters) will be conducted as per the criteria described in Section 2.6 (sampling) and each of the 18 schools will be randomly assigned to either the intervention (with SBSRH package) or the control group (without SBSRH package). This means that both the intervention arm and control arm had will have a total of nine schools each.

Within each school, the 1080 study participants will be selected systematically based on the inclusion criteria described in Section 2.2 (selection criteria). The recruitment of the study participants will be done independently by the researchers and research assistants. This will be done at school using the systematic sampling framework described in Section 2.6. The process is anticipated to take place within one month for all the 18 schools. Only girls who meet the inclusion criteria will be enrolled into the study. The participants will be informed about the study objectives without revealing the study hypotheses. Upon recruitment, each participant with their parent will be required to ascent and consent, respectively, by signing formal ascent and consent forms. Data collection (base line) will be done, an SBSRH package will be provided in the nine intervention clusters (schools) and follow-up is done for 12 months. An end of study assessment will be conducted after twelve months and data will be analyzed.

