#### 2.8.1. Tier 1: In-School ASRH Education Session

The health education sessions will provide information and create awareness on HIV, pregnancy, safer sex, Gender Based Violence, HIV, pregnancy, sexually transmitted infections (STIs), gender norms, effective communication and safe sex practices, sexuality and self-assertion. The Stepping Stones curriculum and the National sexuality framework in Uganda will be used as the standardized behavioral change package using the interpersonal peer to peer approach. 10 sessions (communication, how we act, sex, love, gender based violence, contraceptives, HIV prevention, safer sex practices, assertiveness, supporting one another and self-reflection) will be conducted for the participants by fellow trained peers and knowledge change as well as behavioral change assessed. Implementation of sessions will be done in small groups of 15–20 girls (peers). Peer facilitators will be trained and supported to conduct the small group discussions on SRH and HIV prevention. The researcher, research assistants, SRH nurse and senior woman teacher in-charge of SRH will supervise these sessions.

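### As narrated, schools are allocated before girls are enrolled and only the hypotheses are concealed, so consent can differ by known arm; the draw should follow baseline in all 18 schools

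*Protocol article*

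**What the plan says.** **Allocation.** Section 2.6 (Random Sampling) ties the draw to the choice of schools: "After selection of the 18 schools, nine schools will be randomly allocated to the intervention group". The method is a manual draw: "The names of the 18 selected schools will be placed in a basket and randomly selected and allocated to either group of study". Neither sentence links it to completed enrolment. The Systematic Sampling paragraph comes next: the school administration lists the girls, and 60 per school are taken from class lists at a preset interval of 2.

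**Recruitment.** Section 2.7 keeps that order. It says that "each of the 18 schools will be randomly assigned to either the intervention (with SBSRH package) or the control group (without SBSRH package)". The next paragraph begins "Within each school, the 1080 study participants will be selected systematically". It continues "The recruitment of the study participants will be done independently by the researchers and research assistants", and then "Upon recruitment, each participant with their parent will be required to ascent and consent, respectively, by signing formal ascent and consent forms". Baseline data collection follows, then the package in the nine intervention schools. The Abstract has the same order.

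**Delivery.** Section 2.8.1 says of the peer sessions: "The researcher, research assistants, SRH nurse and senior woman teacher in-charge of SRH will supervise these sessions".

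**Blinding.** Section 2 (Methodology) states an aim about allocation: "Blinding will be done to prevent systematic biases stemming from foreknowledge of group allocations among the participants". The operational text in Sections 2, 2.6 and 2.7 conceals something else, the hypotheses. Section 2.6 also mentions blinding at the random allocation of schools, without saying who is masked or until when.

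**The concern.** Randomising schools balances the schools. It balances the girls only if those who enter the analysis are chosen without reference to arm. If a school's arm is known when families are asked to sign, the question put to them can differ: in one arm, a study that brings peer sessions on sex and contraception and a weekly on-site clinic; in the other, a survey. The protocol's own Introduction reports strong public disagreement about contraceptives in schools, so different consent is plausible here.

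Girls who enrol could then differ between arms in underlying pregnancy risk, and the difference would be read as an intervention effect. Intention-to-treat analysis keeps whoever was enrolled in her school's arm and cannot recover those who declined. Concealing the hypothesis does not help, because arm and hypothesis are different pieces of information.

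**Working it through.** **1. Order of steps.**

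| Place | First | Then |
|---|---|---|
| Abstract | schools selected and allocated 1:1 | girls selected |
| 2.6 | nine schools drawn to each arm | girls listed and sampled |
| 2.7 | schools assigned to package or no package | girls selected, consent and assent, baseline, package |

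All three narrate allocation first. None places the draw after consent or baseline.

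**2. Who knows what.** Research assistants and school administration are blinded to the hypotheses (2.6), and participants are told the objectives but not the hypotheses (2.7). Masking of recruiters, schools or families to the school's arm is not stated. Section 2 therefore aims at a protection that the described procedure does not provide.

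**3. Who does what.** Listing: school administration (2.6). Recruitment: researchers and research assistants (2.7). Session supervision: the researcher and research assistants, among others (2.8.1). Baseline: a self-administered questionnaire (Data Collection Tools, under 2.8.3), with no one named as administering it. The overlap is documented for recruitment and supervision only.

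**4. The plan's sample size, to see whether the fix affects it.**
- (1.96 + 0.842)² × (0.29 × 0.71 + 0.19 × 0.81) / 0.10² = 7.851 × 0.3598 / 0.01 = 282.5 per group (stated 282.5, rounded to 283).
- Design effect 1 + 59 × 0.01 = 1.59; 282.5 × 1.59 = 449 per group, 898 in total; × 1.10 = 988; 988 / 60 = 16.5, taken to 17 and then 18 clusters; 18 × 60 = 1080.

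All of this reproduces. No term depends on when the draw is held.

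**5. What a shift in enrolled risk would do (assumed shifts, not in the documents).** Take 540 girls per arm, so effective size 540 / 1.59 = 339.6, and no true effect. With common risk p, SE = √(2p(1 − p)/339.6), which is 0.0348 at p = 0.29 and 0.0301 at p = 0.19. For a shift b between arms, the two-sided 5% test rejects with probability Φ(−1.96 + b/SE) + Φ(−1.96 − b/SE).

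| Shift b | Rejection at p = 0.29 | Rejection at p = 0.19 |
|---|---|---|
| 0 | 5% | 5% |
| 1 point | 6% | 6% |
| 2 points | 9% | 10% |
| 3 points | 14% | 17% |
| 5 points | 30% | 38% |

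A shift equals the difference between arms in the share of high-risk girls times the risk gap between high-risk and other girls. Assumed share differences of 0.05 to 0.20 and gaps of 0.10 to 0.30 give 0.05 × 0.10 = 0.5 points up to 0.20 × 0.30 = 6 points, in either direction.

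**The case against.** **The order is inferred.** No sentence says outright that girls are enrolled after the draw. In 2.6 both steps hang on the same event, the selection of the 18 schools, and the sampling flow chart (Figure 1) is not available here. A reader might infer that the protocol expressly fixes enrolment after allocation; it does not go that far. What stands is that all three descriptions put allocation first and none says the reverse.

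**Safeguards exist.** Every school must agree to on-site SRH outreach before it is eligible (2.6), so acceptance by the school precedes allocation in both arms. A fixed interval leaves recruiters little room to choose. The clinic is open to every student, enrolled or not (2.8.2), so refusing the study does not keep a girl away from it. Section 2.2 lists parental consent only for ages 15–17, although 2.7 reads more broadly. These points narrow the risk. They do not cover refusal by a girl or parent who knows the arm, nor how refusers are replaced if 60 must be reached.

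**Staff overlap.** A reader might infer that those who supervise the intervention also measure baseline. The documents do not say so.

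**Size.** A reader might want a figure for the spurious benefit. Any such figure depends on assumed consent rates and risks, and the direction could be reversed. A 1-point shift moves the error rate only from 5% to about 6% and is small beside the planned 10-point difference. That is fair: the documents do not show that the bias is large.

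**A condensed article.** The exact timing may stand in the full protocol. But the article itself states both the sequence and the blinding aim, and these do not fit together.

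**Conclusion.** The point holds in a limited form. As written, the sequence lets a school's arm be known when girls and parents decide whether to enrol, and the stated blinding, which covers hypotheses, does not deliver the protection against foreknowledge of allocation named in Section 2. This rests on reading the order of the narrative as the order of events. The bias is possible, not demonstrated, and its size and direction cannot be derived from the documents; the error rates above show only what given shifts would do. The change is worth making because it removes a recognised source of bias at little cost, and because no later analysis can undo differential enrolment.

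**What to change.** In Sections 2.6 and 2.7, state the order explicitly: choose the 18 schools; complete listing, systematic selection, consent or assent and the baseline survey in all 18; then hold the basket draw; add no girl after it. Families in every school then decide without knowing the arm.

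Reword the blinding statements in Sections 2 and 2.6 to say that allocation is unknown to schools, recruiters and participants until baseline is complete; that participants and delivery staff are not masked to arm after that; and that the hypotheses remain concealed from data collectors and analysts. If the intended order is already enrolment first, these sentences are all that is needed.

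Cost: Section 2.7 already plans one month for recruitment in all 18 schools. If baseline fits in that month, the intervention in nine schools starts up to about one month later. The 18 clusters, 1080 girls and power are unchanged.

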## Abstract

Uganda has persistently had high adolescent pregnancy prevalence; 25% for the last 10 years. This protocol presents the design of a Cluster Randomized Controlled Trial (CRCT) to investigate the effectiveness of School-Based Sexual and Reproductive Health (SBSRH) interventions on prevention of pregnancy among school girls aged 15–19 years in the Hoima District, Uganda. 18 secondary schools (clusters) will be selected using cluster sampling and allocated 1:1 into control or intervention group stratified by geographical location. 1080 (60 each cluster) participants/girls aged 15–19 years will be selected using simple random sampling. The intervention group will receive tailored SRH information, in-school medical care and referral over 12 months. The control group will receive no intervention from the research team; however, they can access alternative services elsewhere if they wish. Data will be obtained at baseline, 6 months and 12 months. The outcomes are reduction in occurrence of pregnancy, utilization of SRH services and sexual behavioral change. To our knowledge, this is the first CRCT providing combined SRH interventions for prevention of adolescent pregnancy in Uganda. If effective, it could have great potential in preventing adolescent pregnancy. Trial Registration: Pan African Clinical Trial Registry (PACTR201810882140200) Registered on 16 October 2018.

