#### 2.1.3. Intervening Factors: Age, Religious Beliefs, Family Background, Level of Formal Education and Socio-Economic Status of the Adolescents.

**Study Area:** This study will be conducted in the Hoima District in Bunyoro region, because it is among the top five regions in Uganda with a high percentage of adolescent pregnancies, and hence, it is a representative region. Hoima has a higher percentage of adolescent pregnancies at 29% compared to the national level of 25% [4]. Access (5 km or more) to a public health facility by the population including adolescent girls is limited and it is estimated that approximately 39.5% of the population in the Hoima District live outside the catchment area (5 km or more) of public health facilities. This contributes significantly to inaccessibility and low utilization of SRH care among the adolescents who largely depend on financial support from the parents or guardians. This implies that the adolescent girls may not have the need for ASRH services met due to this hindrance [4].

The District has a thriving oil and tourism economic activities which increase the risk of vulnerability of the adolescent girls to risky sexual behavior. The Hoima District is located in Western Uganda, approximately 230 kilometers from Kampala. The District has a total geographical area of 5735.3 square kilometers and is bordered by Buliisa, Masindi, Kibaale, Kyankwanzi and Ntoroko Districts, and the Democratic Republic of Congo across Lake Albert. The District has a total of 36 registered secondary schools.

**Study Population:** 1080 adolescent girls aged 15–19 years attending secondary school in the Hoima District, Uganda.

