Based on the above logistical regressions, inferential statistics such as t-test and chi square test will be used to determine the similarity in the two groups using their baseline data (baseline comparison) and to determine relationships as well as associations between variables. Chi square tests will be used to test the relationships between categorical variables, while independent t-tests will be carried out to determine differences between the study groups for continuous variables with normal distribution.

Cluster level: The summary measure for each cluster (mean or proportion) will be calculated, because each cluster provides only one data point and the data will be considered to be independent while allowing standard statistical tests to be used. Multiple regressions will be used for the data summarized at the cluster level.

Individual level: During the two stage data analysis process, individual level covariates will be incorporated into the cluster analysis while accounting for the intra-cluster correlation, thus increasing the statistical power of the analysis. Statistical tests will be conducted taking into account for the clustering effect.

Qualitative data collected during the key informant interviews and focus group discussions will be transcribed and typed into a Microsoft Word computer program. These notes will be transcribed verbatim to ensure complete capturing of the responses of the study participants. Thematic analysis will be used to analyze qualitative data from key informant interviews and focus group discussions using the Atlas qualitative data analysis software version 7 (atlasti.com). Themes and sub-themes relevant to the objectives of the study will then be identified to enable development of qualitative coding and code definitions. Codes will be grouped into categories and then themes. The coded transcripts will be analyzed by running query reports and primary documents tables of codes by objective or theme and results will be used to explore the magnitude of the issues from the various focus group discussions and key informant interviews. Quotes illustrating meaning or key messages from the analysis will be selected based on the code count or how illustrative to the theme the quotes will be.

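### The abstract claims allocation stratified by geographical location, but section 2.6 describes one unstratified draw of all 18 schools

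*Protocol article*

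**What the plan says.** The abstract states that the 18 schools are "allocated 1:1 into control or intervention group stratified by geographical location".

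Section 2.6, under Random Sampling, fixes the totals ("nine schools will be randomly allocated to the intervention group and the other nine will be allocated to the control group") and then gives the mechanics: "The names of the 18 selected schools will be placed in a basket and randomly selected and allocated to either group of study". No strata appear there. Section 2 (Methodology), section 2.5 (Number of Clusters) and section 2.7 restate the nine-and-nine assignment without strata; section 2.7, for instance, has "each school will be randomly assigned to the intervention study group or the control study group".

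Geography does enter, but at the step that chooses schools. Section 2.6 says "The District has 36 registered secondary schools in four constituencies Kigorobya, Bugahya, the Hoima municipality and the Buhaguzi counties" and, under Cluster Sampling, "Four to five secondary schools with the highest student enrolment and highest school dropout rates will be selected from each county". It also lists the school's location among the requirements for taking part.

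**The concern.** The two descriptions are different randomisations. Stratified allocation draws separately within each location and controls the split there. One basket controls only the overall 9:9 total. In the abstract the word for stratification qualifies the allocation, so county-wise selection of schools does not make it true: selection spreads the sample over the district but does nothing to spread each county over the arms.

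With 18 randomised units, chance imbalance between arms on a school-level characteristic is likely to be noticeable. The article itself treats place as relevant: its Study Area text ties distance from public facilities to low use of services, and use of services is one of the listed primary outcomes. The allocation method also bears on which analysis is appropriate. It must be settled before the draw, because an imbalance cannot be undone afterwards.

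**Working it through.** **Inputs from the article.** 18 schools, 9 per arm (2.5, 2.6); four counties with four to five schools each (2.6); rates 0.29 and 0.19, two-sided alpha 0.05, ICC 0.01 with a cited range of 0.011–0.094, 60 girls per school (2.4.2).

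**Assumptions.** Strata are the four counties. Four to five schools in each, totalling 18, forces sizes 5, 5, 4 and 4. The share R of between-school variance explained by county is not given, so I use 0 to 75%.

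**The plan's own figure.** The article gives no figure for balance. Its sample size reproduces: 7.851 × 0.3598 / 0.01 = 282.5; × 1.59 = 449; 898 × 1.10 = 988; 988 / 60 = 16.5, raised to 17 and then to 18 schools. It takes no account of stratification and is unaffected by this point.

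**Balance under one basket.** There are C(18,9) = 48,620 equally likely draws.

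- Every county within one school: the counties of four split 2:2, and one county of five splits 3:2 while the other splits 2:3. That is 2 × 10 × 10 × 6 × 6 = 7,200 draws, or 14.8%.
- At least one county wholly in one arm: 9,220 draws by enumeration, 19.0%.
- At least one county with arms differing by three or more schools (4:1, 5:0 or 4:0): 25,420 draws, 52.3%.

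A draw within each county gives the first result every time, and still leaves 7,200 possible allocations.

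**Sensitivity to the strata.** With sizes 4, 4, 4 and 6 the first two figures become 8.9% and 21.8%. If location meant only municipality against the rest, the risk is smaller:

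- Four municipal schools: all in one arm in 2 × C(14,9) / 48,620 = 4,004 / 48,620 = 8.2%; split 2:2 in 6 × 3,432 / 48,620 = 42.4%.
- Five municipal schools: 2 × C(13,9) / 48,620 = 1,430 / 48,620 = 2.9%; split 3:2 or 2:3 in 2 × 10 × 1,716 / 48,620 = 70.6%.

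**Size on the outcome scale.** The mean of p(1−p) is 0.3598 / 2 = 0.1799, so the county variance is 0.1799 × 0.01 × R. Spread over counties of 5, 5, 4 and 4, its expected finite variance among the 18 schools is (18/17) × (1 − 82/324) = 0.791 times that. The chance difference between arms due to county has SD √(0.791 × 0.1799 × 0.01 × R × 2/9): 0.9 percentage points at R = 25% and 1.3 at R = 50%, against a planned effect of 10 points.

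**Power.** For a comparison of school proportions, SE² = 0.3598 × [(1 − ρ)/60 + ρ(1 − R)] / 9, with power from the non-central t distribution. Without a county term there are 16 df (critical t 2.12); with it, 13 df (critical t 2.16).

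- ρ = 0.01, no county term: SE² = 0.3598 × 0.0265 / 9 = 0.00106, SE 0.0325, power 0.82.
- ρ = 0.01, county term, R = 50%: SE² = 0.3598 × 0.0215 / 9 = 0.00086, SE 0.0293, power 0.88.

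| ICC | No county term | County term, R = 0 | R = 25% | R = 50% | R = 75% |
|---|---|---|---|---|---|
| 0.01 | 0.82 | 0.81 | 0.85 | 0.88 | 0.92 |
| 0.05 | 0.45 | 0.44 | 0.52 | 0.63 | 0.78 |
| 0.094 | 0.30 | 0.29 | 0.35 | 0.46 | 0.65 |

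**The case against.** An unrestricted 9:9 draw of schools is a proper randomisation, unbiased over draws, with type I error preserved by a suitable cluster analysis. That stands. Counts of schools per county do not by themselves show a biased or weaker result, and at the planned ICC the chance county difference is small beside the planned effect.

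The county layout is also not settled. Section 2.6 speaks both of a per-county quota and of the 18 schools in the district with the highest dropout, and location is never defined as county. The abstract may simply echo county-wise selection, and the sampling flow chart is not available to check. This limits how firmly the percentages can be stated. It does not remove the contradiction: if the abstract meant selection, it misdescribes the allocation and needs correcting.

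A reader might infer that the analysis will ignore location, with standard errors too large as a result. The documents do not support that. The list of intervening factors ("Age, Religious Beliefs, Family Background, Level of Formal Education and Socio-Economic Status of the Adolescents") does not include location, and section 3 says only "Multiple regressions will be used for the data summarized at the cluster level", but neither closes the set of model terms, and stratum terms are commonly left to an analysis plan, which is not shown. The inflated standard error would arise only if stratification were done and then ignored, which is not the procedure described.

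A reader might also infer that oil and tourism activity or distance to care will be confounded with arm. The article describes the former for the district as a whole, and section 2.6 already requires a functioning public health centre within 5–10 km of each school.

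**Conclusion.** The point holds as a contradiction about how the trial is randomised: the abstract claims stratification and the only stated procedure does not provide it. That rests on the text alone.

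The consequence is a lost guarantee of geographic balance, not a certain imbalance or an invalid trial. With counties of 5, 5, 4 and 4, the single draw balances all four to within one school about 15% of the time and leaves a whole county in one arm about 19% of the time; other definitions of location change these figures. The gain in power from stratifying and adjusting is modest at ICC 0.01, slightly negative if county explains nothing, and larger at higher ICC. Its size cannot be fixed from the article, because the county share of variance is not given.

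**What to change.** Before the draw, define the location strata; the four counties already used for selection are the obvious choice. Replace the single basket with one draw per stratum: 2:2 in counties of four, and 3:2 in one county of five with 2:3 in the other, the order drawn at random. This keeps 9:9 overall. If selection gives other county sizes, write the rule for odd counts beforehand. Include the stratum in the primary analysis, and make the abstract and sections 2.6 and 2.7 agree.

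The field cost is four baskets instead of one. The analysis cost is 3 of 16 df, moving the critical t from 2.12 to 2.16.

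If the single basket is kept, remove the stratification claim from the abstract. That also resolves the contradiction, at no cost beyond the edit, but leaves geographic balance to chance.
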